## Abstract

**Introduction:**

Neonatal stroke remains a primary cause of permanent neurological disability. While global prognostic frameworks, including magnetic resonance imaging (MRI) of the posterior limb of the internal capsule (PLIC), General Movements Assessment (GMA), and the Hammersmith Infant Neurological Examination (HINE), have been established to predict motor outcomes, these tools have not been systematically integrated into large-scale Chinese clinical registries. In regions like Shenzhen, the scarcity of prospective, multicenter data continues to hinder the characterization of stroke incidence, risk factors, and long-term outcomes. This protocol details the establishment of the first dedicated online registry in Shenzhen to address these critical evidence gaps.

**Methods and analysis:**

This multicenter, prospective, observational cohort study aims to enroll 300 neonates diagnosed with stroke, including arterial ischemic, hemorrhagic, and cerebral venous sinus thrombosis subtypes from a network of 22 hospitals in Shenzhen, China, between January 2025 and December 2030. Data collection will utilize standardized electronic case report forms (eCRFs), initially managed via a uniform digital system (
Supplementary File 1), with a planned transition to a secure web-based registry for broader access. Participants will undergo longitudinal follow-up until age five, with neurodevelopmental outcomes assessed using the Bayley Scales of Infant and Toddler Development (4th Ed., Chinese Version), 3T cranial MRI, and video-EEG. To explore the metabolic-inflammatory nexus of neonatal injury, placental pathology will be integrated into the clinical data, and a biobank of stool and breast milk samples will be established. The primary outcome is the registry-based incidence of neonatal stroke. In contrast, secondary outcomes include characterizing clinical subtypes, identifying prenatal/perinatal risk factors, and developing and internally validating a robust prognostic prediction model.

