## Introduction

1

Neonatal stroke, defined as an acute focal neurological injury secondary to arterial ischemic infarction, hemorrhagic stroke, or cerebral venous sinus thrombosis occurring between birth and 28 days of life, is a leading cause of permanent neurological disability in infants (1, 2). This cerebrovascular event results in lifelong sequelae such as cerebral palsy, epilepsy, and cognitive impairments, with an estimated incidence ranging from 1 in 1,100 to 1 in 4,000 live births for perinatal stroke; the incidence of strictly neonatal stroke is less well defined but is approximately 1 in 3,000 to 1 in 5,000 live births (3–5) Critically, mortality rates range from 4% to 10%, underscoring its Status as a primary pediatric health concern (6, 7). Despite its profound impact, evidence-based strategies for prevention, acute management, and long-term prognostication remain significantly underdeveloped, with no standardized, population-based surveillance and outcome-tracking systems in many regions.

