A central barrier to improving care is the profound lack of prospective, high-quality data on disease epidemiology and natural history (8). While countries such as the United Kingdom, Canada, and Australia have established national neonatal stroke registries to provide continuous, standardized monitoring of aetiology and outcomes (9, 10), such systematic data-collection initiatives are absent in China. Several other countries have successfully developed neonatal and infantile thrombosis registries; for example, the Italian Registry of Infantile Thrombosis (RITI) has provided valuable lessons regarding multicenter collaboration, data standardization, and the challenges of prospective data collection (9). Fragmented, retrospective studies and significant discrepancies in reported incidence rates characterize the existing evidence. For instance, a multicenter study in Beijing reported a rate of 1 in 2,660 (10), whereas a retrospective review across Shenzhen reported a much lower rate of 1 in 8,373 (10). These discrepancies likely reflect differences in case ascertainment (active surveillance vs. retrospective chart review), imaging protocols (universal MRI vs. selective cranial ultrasound), and referral patterns to tertiary centres, rather than true geographic variation in disease frequency. Furthermore, the long-term neurodevelopmental trajectory for survivors, a critical endpoint for families and healthcare systems, is poorly documented, and clinical management, especially for hemorrhagic and venous stroke subtypes, lacks consensus guidelines, leading to potentially inconsistent care.

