Prognostication of motor outcome following neonatal stroke has been an active area of research. Magnetic resonance imaging (MRI) assessment of the posterior limb of the internal capsule (PLIC) has been shown to correlate with the development of hemiparesis (11, 12). Quantitative scoring systems such as the Modified Pediatric ASPECTS have also been developed to correlate infarct volume with clinical outcomes (13). Additionally, the Hammersmith Infant Neurological Examination (HINE) and general movements evaluation are validated tools for early prediction of cerebral palsy (12). We acknowledge that this registry enrols only diagnosed cases; therefore, cumulative incidence will be calculated using total live births from all 22 participating hospitals as the denominator. However, this represents a hospital-based cohort rather than true population-based surveillance, and referral patterns may bias incidence estimates.

Shenzhen is particularly suitable as a model region due to its annual birth rate of approximately 200,000 live births, >98% NICU coverage across all districts, universal availability of cranial MRI and video-EEG at all participating hospitals, and the fact that >95% of regional births occur within the 22 study hospitals.

Therefore, establishing a prospective, multicenter cohort and dedicated registry is an urgent and foundational step. Such a resource is essential for accurately defining the disease burden, identifying associations with prenatal and perinatal factors that may inform future interventional studies, and mapping the evolution of neurodevelopmental outcomes from infancy through early childhood. By capturing comprehensive, longitudinal data within a real-world clinical setting, a registry can bridge the critical evidence gap between isolated clinical observations and population-level understanding.

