### Study design

2.2

This multicenter, prospective, observational cohort study aims to investigate the long-term neurodevelopmental outcomes of neonates with stroke. The study is planned to run for six years, from January 2025 to December 2030, in Shenzhen, China. The initial network comprises 22 collaborating hospitals, with Shenzhen Children's Hospital as the lead institution and Shenzhen People's Hospital as the primary coordinating center.

The study aims to recruit 300 neonates diagnosed with neonatal stroke, following them prospectively for five years to assess their neurodevelopmental trajectory. Additional hospitals may be included throughout the study period. A detailed study flow diagram is presented in Figure 1.

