### Sample size calculation

2.6

Assuming a 30% neurodevelopmental outcome rate at 5 years (based on published literature), a final sample of approximately 210 evaluable participants would yield 60–80 outcome events. With a maximum of 6–8 candidate predictors, this yields an events-per-variable ratio of approximately 10, exceeding the recommended minimum for logistic regression to avoid overfitting. Internal validation will be performed using bootstrap resampling (1,000 repetitions) to estimate optimism-corrected performance. Total enrollment of 300 accounts, with 10% mortality and 20% loss to follow-up, and the understanding that the final evaluable sample will be approximately 210 participants.

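### Section 2.6 supports about 63 events rather than 60–80, so events per variable is 7.9 at eight predictors; the target of 300 is attainable but depends heavily on the incidence assumed

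*Protocol article*

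**What the plan says.** The abstract says that the study "aims to enroll 300 neonates diagnosed with stroke". Section 2.6 (Sample size calculation) is where that figure is derived. It assumes a 30% outcome rate at 5 years and states that "a final sample of approximately 210 evaluable participants would yield 60–80 outcome events". It allows at most 6–8 candidate predictors, puts events per variable at about 10, and describes that as above the recommended minimum. Deaths of 10% and follow-up losses of 20% then link 210 evaluable to 300 enrolled. Neither births nor incidence enters the derivation.

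The inputs for an accrual check stand elsewhere in the article. The Introduction gives Shenzhen an "annual birth rate of approximately 200,000 live births" and says that ">95% of regional births occur within the 22 study hospitals". It puts strictly neonatal stroke at "approximately 1 in 3,000 to 1 in 5,000 live births", cites a Beijing multicentre rate of 1 in 2,660, and notes that "a retrospective review across Shenzhen reported a much lower rate of 1 in 8,373". It attributes the Beijing–Shenzhen gap mainly to case finding, imaging practice and referral, not to a real regional difference.

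On timing, section 2.2 (Study design) says: "The study is planned to run for six years, from January 2025 to December 2030, in Shenzhen, China". The abstract gives the same dates for enrolment and follows children to age five.

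**The concern.** Section 2.6 rests the design of the prediction model on one property, an events-per-variable ratio of about 10. That property depends on three things: reaching 300, having every enrolled birth year assessed at age 5, and the event count following from the stated 30%. The first is not tested against the protocol's own figures, the second sits uneasily with the end date, and the third fails at the upper end of the stated range.

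At stake is the performance of the prognostic model, a secondary outcome in section 2.5.2. If the candidate list is fixed at eight while events number 63 or fewer, the model starts with less information per parameter than the protocol claims. The primary outcome, incidence, is not invalidated by fewer cases; its interval would only be wider.

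**Working it through.** **1. The plan's own figure.** Inputs from section 2.6: 300 enrolled, 10% deaths, 20% lost, 30% outcome rate, 6–8 predictors.

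- Evaluable: 300 × (1 − 0.10 − 0.20) = 210. This reproduces. Applying the losses in sequence gives 300 × 0.9 × 0.8 = 216, which is close.
- Events: 210 × 0.30 = 63 (216 × 0.30 = 64.8).
- Outcome rate implied by 80 events: 80/210 = 38%. The upper end of 60–80 does not follow from 30%.
- Events per variable: 63/6 = 10.5; 63/8 = 7.9. With 216 evaluable: 10.8 and 8.1.

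A ratio of 10 at both ends appears only if 60 events are paired with six predictors and 80 events with eight. The 80 is not supported, so neither is the second pairing.

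**2. Accrual from the Introduction's inputs.** Births over six years: 200,000 × 0.95 × 6 = 1,140,000. Cases = births × incidence; evaluable = 0.70 × cases; events = 0.30 × evaluable. The table takes every case as enrolled and followed to age 5.

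| Incidence | Source | Cases | Evaluable | Events | Per variable at 6 | Per variable at 8 |
|---|---|---|---|---|---|---|
| 1 in 8,373 | Shenzhen, retrospective | 136 | 95 | 29 | 4.8 | 3.6 |
| 1 in 5,000 | neonatal range, low end | 228 | 160 | 48 | 8.0 | 6.0 |
| 1 in 3,800 | rate needed for 300 | 300 | 210 | 63 | 10.5 | 7.9 |
| 1 in 3,000 | neonatal range, high end | 380 | 266 | 80 | 13.3 | 10.0 |
| 1 in 2,660 | Beijing | 429 | 300 | 90 | 15.0 | 11.3 |

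Required rate: 1,140,000/300 = 3,800, so one enrolled infant per 3,800 births. If all 200,000 annual births counted, it would be 1,200,000/300 = 4,000.

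**3. Share of cases that must be enrolled.** At 1 in 3,000: 300/380 = 79%. At 1 in 2,660: 300/429 = 70%. At 1 in 5,000: 300/228 = 132%, which is not possible. The protocol states no eligible-and-consented share.

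**4. Timing.** The event column needs all six birth years to reach age 5. If age-5 assessments had to be complete by December 2030, only about the first birth year would contribute:

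- 190,000/5,000 = 38 cases, and 38 × 0.70 × 0.30 = 8 events
- 190,000/3,000 = 63 cases, and 63 × 0.70 × 0.30 = 13 events

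The abstract can be read as ending only enrolment in December 2030; section 2.2 gives that date as the end of the study.

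**The case against.** **The Shenzhen rate is not a forecast.** A reader might infer that the registry will find about 136 cases and 29 events. The documents do not support that. The Introduction treats the retrospective rate as probably affected by ascertainment, whereas this study is prospective, requires MRI confirmation and screens infants with risk factors by MRI (section 2.3.1). The general neonatal range gives 228–380 cases, which brackets 300. This stands: the Shenzhen rate is a pessimistic case only.

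**300 is not a miscalculation.** Working back from a model requirement is legitimate, and 210/0.70 = 300 is correct. An accrual forecast may also sit in a full protocol that is not shown. This stands too: its absence from the article is not in itself an error. The mismatch between 30%, 210 and 80 events is inside section 2.6 and does not depend on any forecast.

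**The case counts are not strict upper limits.** Section 2.2 allows more hospitals, 95% is a floor, and referrals may add cases. Nor do we know whether the published rates already leave out silent or ineligible infants, so deducting them could count them twice. This stands in part. Adding hospitals within Shenzhen can raise births by only about 5% (200,000/190,000), and refused consent lowers enrolment whatever the rate.

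**The model has safeguards.** A reader might infer that it will be badly overfitted and that nothing protects it. That goes too far. The 6–8 is a ceiling, section 2.7 selects predictors by LASSO, and a bootstrap of 1,000 resamples is planned to correct for optimism. These limit and measure overfitting, but they supply no events and do not make the stated ratio true.

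**Conclusion.** The point holds in two parts of different strength.

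The firm part is internal to section 2.6. With full accrual and the stated 30%, about 63 events are expected, not up to 80. The ratio is 10.5 at six predictors and 7.9 at eight, so the claimed property fails at the upper predictor count and has almost no slack at the lower one. This rests only on the protocol's own inputs.

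The conditional part is accrual. The target of 300 is attainable but rate-sensitive: the quoted rates span 136–429 cases and 29–90 events, and 228–380 cases within the general neonatal range. These figures assume six full years of births, 95% coverage, every case enrolled, and every birth year assessed at age 5. The last assumption has to be reconciled with the December 2030 end date. Nothing in the documents shows that 300 cannot be reached.

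The consequence falls on a secondary outcome. The section should be corrected, but the point does not threaten the primary incidence estimate.

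**What to change.** In section 2.6:

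- Restate expected events as about 63 at full accrual, with 10.5 events per variable at six predictors and 7.9 at eight.
- Add the accrual calculation, births × coverage × incidence × share eligible and consented, with the assumed share stated. Show the range of cases, give the Shenzhen rate as the pessimistic case, and say that 300 means one enrolled infant per 3,800 births.
- State whether December 2030 ends enrolment or the whole study, align section 2.2 and the abstract, and base the event count on the birth years that will reach age 5.
- Replace the fixed 6–8 predictors by a rule set before modelling: candidate parameters entering LASSO do not exceed observed events divided by 10. That is about 6 at 63 events, 4 at 48 and 2–3 at 29. The divisor follows the ratio of about 10 on which the protocol already relies.

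The cost is a few lines of text, a less favourable stated figure and possibly a smaller model. No additional enrolment is needed.

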**Clinical Trial Registration:**
https://www.chictr.org.cn, identifier ChiCTR2500097104.

## Introduction

1

Neonatal stroke, defined as an acute focal neurological injury secondary to arterial ischemic infarction, hemorrhagic stroke, or cerebral venous sinus thrombosis occurring between birth and 28 days of life, is a leading cause of permanent neurological disability in infants (1, 2). This cerebrovascular event results in lifelong sequelae such as cerebral palsy, epilepsy, and cognitive impairments, with an estimated incidence ranging from 1 in 1,100 to 1 in 4,000 live births for perinatal stroke; the incidence of strictly neonatal stroke is less well defined but is approximately 1 in 3,000 to 1 in 5,000 live births (3–5) Critically, mortality rates range from 4% to 10%, underscoring its Status as a primary pediatric health concern (6, 7). Despite its profound impact, evidence-based strategies for prevention, acute management, and long-term prognostication remain significantly underdeveloped, with no standardized, population-based surveillance and outcome-tracking systems in many regions.

A central barrier to improving care is the profound lack of prospective, high-quality data on disease epidemiology and natural history (8). While countries such as the United Kingdom, Canada, and Australia have established national neonatal stroke registries to provide continuous, standardized monitoring of aetiology and outcomes (9, 10), such systematic data-collection initiatives are absent in China. Several other countries have successfully developed neonatal and infantile thrombosis registries; for example, the Italian Registry of Infantile Thrombosis (RITI) has provided valuable lessons regarding multicenter collaboration, data standardization, and the challenges of prospective data collection (9). Fragmented, retrospective studies and significant discrepancies in reported incidence rates characterize the existing evidence. For instance, a multicenter study in Beijing reported a rate of 1 in 2,660 (10), whereas a retrospective review across Shenzhen reported a much lower rate of 1 in 8,373 (10). These discrepancies likely reflect differences in case ascertainment (active surveillance vs. retrospective chart review), imaging protocols (universal MRI vs. selective cranial ultrasound), and referral patterns to tertiary centres, rather than true geographic variation in disease frequency. Furthermore, the long-term neurodevelopmental trajectory for survivors, a critical endpoint for families and healthcare systems, is poorly documented, and clinical management, especially for hemorrhagic and venous stroke subtypes, lacks consensus guidelines, leading to potentially inconsistent care.

Prognostication of motor outcome following neonatal stroke has been an active area of research. Magnetic resonance imaging (MRI) assessment of the posterior limb of the internal capsule (PLIC) has been shown to correlate with the development of hemiparesis (11, 12). Quantitative scoring systems such as the Modified Pediatric ASPECTS have also been developed to correlate infarct volume with clinical outcomes (13). Additionally, the Hammersmith Infant Neurological Examination (HINE) and general movements evaluation are validated tools for early prediction of cerebral palsy (12). We acknowledge that this registry enrols only diagnosed cases; therefore, cumulative incidence will be calculated using total live births from all 22 participating hospitals as the denominator. However, this represents a hospital-based cohort rather than true population-based surveillance, and referral patterns may bias incidence estimates.

Shenzhen is particularly suitable as a model region due to its annual birth rate of approximately 200,000 live births, >98% NICU coverage across all districts, universal availability of cranial MRI and video-EEG at all participating hospitals, and the fact that >95% of regional births occur within the 22 study hospitals.

Therefore, establishing a prospective, multicenter cohort and dedicated registry is an urgent and foundational step. Such a resource is essential for accurately defining the disease burden, identifying associations with prenatal and perinatal factors that may inform future interventional studies, and mapping the evolution of neurodevelopmental outcomes from infancy through early childhood. By capturing comprehensive, longitudinal data within a real-world clinical setting, a registry can bridge the critical evidence gap between isolated clinical observations and population-level understanding.

To address this unmet need, we have designed the Shenzhen Neonatal Stroke Online Registry. In this study, we hypothesize that implementing a standardized, multicenter, prospective cohort will yield accurate epidemiological data, identify key risk factors associated with adverse outcomes, and establish a robust platform for developing prognostic models. We present the protocol for a six-year, prospective, observational cohort study involving 22 hospitals in Shenzhen. The primary objectives are to determine the registry-based incidence of neonatal stroke and to evaluate comprehensive neurodevelopmental outcomes at 5 years of age. Secondary objectives include characterizing stroke subtypes, analyzing current management disparities, and integrating a biobank for future mechanistic research. This protocol aims to provide a replicable model for disease surveillance and to generate high-quality evidence to inform clinical guidelines, optimize care pathways, and ultimately improve long-term outcomes for infants affected by stroke.

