#### Inclusion criteria

2.3.1

Participants must meet all the following criteria:
Gestational age ≥28 weeks and ≤28 days postnatal, with identified stroke risk factors. (Extremely preterm infants <28 weeks are excluded by design due to diagnostic challenges and different pathophysiology.Clinical presentation of acute encephalopathy or seizures.Neuroimaging confirmation (MRI) of stroke (arterial ischemic, hemorrhagic, or cerebral venous sinus thrombosis), excluding other common etiologies. Clinically silent infarctions (incidental findings on imaging without clinical symptoms) will be excluded. To ensure complete case ascertainment, all neonates with identified risk factors for stroke (e.g., congenital heart disease, extracorporeal membrane oxygenation, or severe perinatal asphyxia) will undergo systematic screening with cranial MRI, and any asymptomatic infarctions detected will be documented separately but excluded from the primary analysis cohort**.**Parental or legal guardian consent.

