#### Exclusion criteria

2.3.2

Participants will be excluded for any of the following:
Congenital structural brain malformations.Seizures attributable to a metabolic cause (e.g., electrolyte imbalances or hypoglycemia).Transfer to a non-participating center or voluntary discharge prior to enrollment.Refusal of informed consent by the parent or guardian.

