#### Recruitment, screening, and informed consent

2.4.1

Neonates meeting the inclusion criteria will be prospectively identified and recruited by trained neonatologists from the NICUs and pediatric wards of the 22 participating hospitals. Two attending neonatologists at each site will be responsible for patient enrollment using standardized diagnostic criteria.

Written informed consent will be obtained from the parents or legal guardians after a definitive diagnosis is made. The study adheres to the ethical principles of the Declaration of Helsinki and has received institutional ethics approval.

To ensure rigorous standardization across the 22 participating centres, all enrolling neonatologists will undergo a mandatory centralized training workshop focused on standardized case definitions, MRI interpretation using a validated study atlas, and EEG acquisition protocols. In parallel, to maintain longitudinal data quality, annual inter-rater reliability assessments will be conducted using 10 blinded test cases. For diagnostic adjudication, all stroke subtypes will be centrally reviewed by an expert committee comprising three senior neonatologists and two neuroradiologists at Shenzhen Children's Hospital, who remain blinded to the initial site-level diagnosis. Furthermore, neuroimaging will adhere to a harmonized 3T MRI protocol (including DWI, SWI, and MRA/MRV sequences). Where 3T MRI is not immediately available at a participating center, arrangements will be made for patient transfer to a center with 3T capacity, and this will be documented. Specific scoring approaches for infarct volume (modified Pediatric ASPECTS) and PLIC assessment will be used centrally. All video-EEG recordings will be centrally interpreted by a single epileptologist masked to all clinical and imaging data.

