#### Data elements and database modules

2.4.3

The online registry is divided into the following modules:
General and Hospital Information: Demographics, birth facility data, and administrative details.Family and Perinatal History: Family history, maternal/pregnancy data, labor/delivery details, and resuscitation history.Neonatal Clinical Presentation: Initial Status (e.g., blood glucose), seizure data, and comorbidities.Diagnostic Tests and Biological Samples: Coagulation tests, genetic data (optional), neuroimaging, and EEG results.Treatment and Discharge Summary: Details of therapies, discharge diagnosis, and treatment outcomes.Long-Term Follow-up Examinations: Data from 6m, 18m, 3y, and 5y visits, including Bayley-4C scores, EEG, MRI results, growth metrics, and epilepsy medication.Follow-up Conclusions: Final Status, including outcomes like epilepsy, cognitive impairment, motor disorders, and cerebral palsy, confirmed by pediatric neurologists and rehabilitation physicians.The complete data dictionary is available in Online Supplementary File 3.

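### The incidence numerator is limited to consented, enrolled cases of at least 28 weeks, but the denominator is all live births in the 22 hospitals

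*Protocol article*

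**What the plan says.** **Denominator.** The Introduction states that "cumulative incidence will be calculated using total live births from all 22 participating hospitals as the denominator". It sets no lower limit of gestation for these births.

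**Numerator.** No sentence defines the incidence numerator separately. The same Introduction paragraph says "We acknowledge that this registry enrols only diagnosed cases", and the enrolled case is the only case definition given. To be enrolled, an infant must:

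- have a gestational age of at least 28 weeks (section 2.3.1);
- have "Parental or legal guardian consent" (section 2.3.1), sought after a definitive diagnosis (section 2.4.1);
- not fall under the exclusions "Transfer to a non-participating center or voluntary discharge prior to enrollment" or "Refusal of informed consent by the parent or guardian" (section 2.3.2).

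**Where cases are found.** Section 2.4.1 recruits "from the NICUs and pediatric wards of the 22 participating hospitals", that is, by place of treatment. Neither section 2.3.1 nor section 2.3.2 has a birthplace criterion. Section 2.4.3 does record "Demographics, birth facility data, and administrative details".

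**Role of the estimate.** Registry-based incidence is the only entry under Primary outcomes (section 2.5.1). The Introduction warns that referral patterns may bias it. It does not mention loss through consent or exit before enrolment.

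**The concern.** An incidence proportion needs a numerator drawn from the infants counted in its denominator, with every case among them having the chance to be counted. Here the two sets are built by different rules. Refusals, transfers out and voluntary discharges remove cases but not births. Births under 28 weeks add to the denominator but cannot supply a case. In the other direction, an infant born outside the network and treated inside it would add a case without a birth.

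The Introduction attributes the gap between the two earlier Chinese rates (1 in 2,660 and 1 in 8,373) largely to differences in case ascertainment, imaging and referral. A registry set up to settle that question should not carry an unmeasured ascertainment loss of its own. The loss also cannot be repaired at the end of the study, because cases that were never logged cannot be recovered by analysis.

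**Working it through.** **1. The plan's own figures.** The sample size section gives no expected incidence or precision for the primary outcome. Its one calculation concerns the follow-up cohort and reproduces: 300 × (1 − 0.10 − 0.20) = 210 evaluable, and 210 × 0.30 = 63 events, within the stated 60–80.

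**2. Scale of the incidence estimate.** Inputs from the Introduction: about 200,000 births a year and over 95% of regional births in the 22 hospitals. From section 2.2: January 2025 to December 2030 and 300 cases. If recruitment fills all six years:

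- births: 200,000 × 0.95 × 6 = 1,140,000;
- implied incidence: 300 / 1,140,000 = 1 in 3,800;
- exact Poisson 95% limits for 300 cases: 1 in 3,393 to 1 in 4,270, which is about −11% to +12% on the incidence scale.

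**3. Bias formula.** Let *c* be the share of eligible inborn cases that are enrolled, and *o* the share of enrolled cases born outside the 22 hospitals. Then

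reported / true = *c* / (1 − *o*).

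The documents give neither *c* nor *o*.

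**4. Loss before enrolment alone (*o* = 0).** Assume *c* = 0.80 to 0.95, and for illustration a true incidence of 1 in 4,000, which lies inside the Introduction's range of 1 in 3,000 to 1 in 5,000.

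| *c* (assumed) | reported / true | true 1 in 4,000 is reported as |
|---|---|---|
| 0.95 | 0.95 | 4,000 / 0.95 = 1 in 4,211 |
| 0.90 | 0.90 | 4,000 / 0.90 = 1 in 4,444 |
| 0.80 | 0.80 | 4,000 / 0.80 = 1 in 5,000 |

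**5. Adding outborn cases from the region.** Under 5% of regional births fall outside the network. If those infants have the same risk and all their cases reach a study hospital, *o* is at most 0.05, and the inflation factor is at most 1 / 0.95 = 1.053.

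- Lowest ratio: 0.80 / 1.00 = 0.80.
- Highest ratio: 0.95 / 0.95 = 1.00.

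**6. Births under 28 weeks.** If a fraction *p* of births is below 28 weeks, incidence among births of at least 28 weeks is understated by a further factor of 1 − *p*. The document gives no *p*, so this is left out of the range above and treated as secondary.

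**7. Against sampling error.** At *c* = 0.80 the bias is −20%, larger than the −11% sampling limit. At *c* = 0.90 it is −10%, about the same size. At *c* = 0.95 it is smaller.

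**The case against.** The best defence is that the outcome is deliberately called registry-based, that the Introduction concedes the cohort is hospital-based and open to referral bias, and that birth facility is recorded, so an analysis plan could restrict to inborn cases. This stands for the outborn component. It does not cover consent refusal and exit before enrolment, which are not named as a bias on incidence and which no later analysis can restore without a log.

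A second defence is that birth coverage above 95% keeps outborn cases few. That also stands. A reader might infer that the bias runs strongly in both directions: an outborn share of 20% with 95% enrolment would give 0.95 / 0.80 = 1.19. The documents do not support this. A ratio above 1 needs referral from outside the region or of higher-risk infants, for which no figure is given, though nothing excludes it. That outborn infants enter at all is itself inferred from recruitment by treatment site and the absence of a birthplace rule. Likewise, loss of infants who die before consent is possible, but no text says that such families cannot consent.

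A reader might also object that "Additional hospitals may be included throughout the study period" comes without a rule for when a new hospital's births start to count, or that hospital level in the stratified rates is not tied to the birth hospital or the treating hospital. Both are details commonly left to a full protocol or analysis plan and are not part of this point.

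Finally, births under 28 weeks are excluded as cases by design. Section 2.7 already stratifies incidence by gestational age, so the matching denominator should be obtainable. This makes that part easy to correct and probably minor.

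**Conclusion.** The point holds. As written, the primary incidence estimate divides consented and enrolled cases by births that were subject to neither condition, and the resulting downward bias is not disclosed. With 80–95% of eligible cases enrolled, reported/true incidence is 0.80 to 0.95 without outborn cases, and 0.80 to 1.00 once in-region outborn cases at equal risk are allowed for. At the lower end the bias exceeds the random error from 300 cases.

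The structural mismatch comes directly from the text and does not depend on these numbers. The size does: the enrolment share is an assumption, and the 1.05 ceiling rests on the stated coverage and on equal risk. A net upward bias is not shown.

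**What to change.** Define the incidence numerator separately from the consented cohort:

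- **Numerator:** all centrally confirmed strokes that meet the clinical and imaging criteria in infants born at 28 weeks or more in a participating hospital, whether or not they were consented or enrolled. Use the recorded birth facility for enrolled cases, and an anonymous screening log for those refused, transferred out or discharged before enrolment, subject to ethics approval.
- **Denominator:** live births at 28 weeks or more in the same hospitals over the same period.
- **Outborn cases:** report them separately, outside the incidence numerator.
- **Reporting:** state the number of eligible cases logged and the share enrolled, so that the size of the loss is visible.

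Follow-up and the prediction model keep the consented cohort unchanged.

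The cost is an ethics note for anonymous counts, a short log at each site and a few sentences of analysis wording. Some outborn cases leave the incidence numerator. The log should start as early as possible, since recruitment was planned from January 2025 and cases missed before it begins may not be recoverable.
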